## 1.0 INTRODUCTION

The RESCUEicp trial protocol (Version 6, dated August 2015) describes the study design. The purpose of this Statistical Analysis Plan is to give a more detailed and comprehensive description of the methods for the analysis of the trial data, to avoid post hoc decisions that may affect the interpretation of the results of the statistical analysis.

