### 2.1 Clinical Outcome Measures as Specified in the Trial Protocol (Version 6, dated August 2015)

1. The primary endpoint is the Extended Glasgow Outcome Scale (GOSE) at 6 months after randomisation.
2. The secondary endpoints are:
  - a. GOSE at 12 and 24 months after randomisation
  - b. Mortality at 6, 12 and 24 months after randomisation
  - c. SF-36 and SF-10 (below 16 years) questionnaires at 6, 12 and 24 months after randomisation
  - d. Glasgow Coma Scale (GCS) at discharge from neurosciences hospital
  - e. Assessment of ICP control
  - f. Time in intensive care
  - g. Time to discharge from the neurosciences hospital
  - h. Detailed health-economic analysis

Adverse events will also be reported.

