#### **4.2 Primary Outcome Measure**

The primary outcome measure will be the extended Glasgow Outcome Scale (GOSE) evaluated at six months. The main analysis will be an ordinal analysis based on the proportional odds model, with the result presented as the estimated common odds ratio with its corresponding 95% confidence interval and p-value. For this primary analysis the GOSE categories of upper good recovery and lower good recovery will be pooled since a blinded review of the distribution of GOSE revealed that there are too few patients in these categories to allow them to be analysed as separate categories.

The goodness-of-fit of this unadjusted proportional odds model will be tested. If the proportional odds model is rejected at the 5% significance level then that in itself will mean that there is evidence of a difference in the distribution of the GOSE scores between the two randomised groups, and the interpretation of the results will focus on describing the difference.

As a sensitivity analysis the proportion of patients achieving a 'favourable' outcome (defined as upper severe disability or better on the GOSE scale) will be compared between the randomised groups using a chi-squared test. The result will be presented as the estimated odds ratio with its corresponding 95% confidence interval and p-value, for comparison with the estimated common odds ratio, and also as the estimated absolute difference in the proportions with the corresponding 95% confidence interval.

Further exploratory analyses will examine the impact of covariate adjustment on the above analyses using ordinal and binary logistic regression respectively. Age, GCS motor score, pupils, and the last available pre-randomisation Marshall CT class will be taken as covariates. Three separate analyses will be undertaken as the GCS motor score and pupils have been recorded at three time points (initial, on arrival at the first hospital, on arrival at the neurosciences hospital). Mean/median value imputation will be used to allow the small proportion of patients with missing values for their baseline covariates to be included in these analyses.

The Glasgow Coma Scale sum at discharge will be analysed using the same ordinal methodology described above for the GOSE. If necessary, adjacent categories will be pooled if there are too few patients with any particular GCS.

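### If proportional odds is rejected, SAP section 4.2 does not say which estimate carries the primary conclusion or how direction and benefit are judged

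*SAP*

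**What the plan says.** Section 2.1 sets the endpoint: "The primary endpoint is the Extended Glasgow Outcome Scale (GOSE) at 6 months after randomisation". Section 4.2 sets the analysis: "The main analysis will be an ordinal analysis based on the proportional odds model, with the result presented as the estimated common odds ratio", with a 95% confidence interval and p-value. In this analysis "the GOSE categories of upper good recovery and lower good recovery will be pooled".

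The fit of the unadjusted model is tested at the 5% level. Of a rejection, the SAP says "that in itself will mean that there is evidence of a difference in the distribution of the GOSE scores between the two randomised groups". On how the trial is to be read in that case, it offers only this: "the interpretation of the results will focus on describing the difference".

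The next paragraph does not depend on the fit test. It begins "As a sensitivity analysis the proportion of patients achieving a 'favourable' outcome (defined as upper severe disability or better on the GOSE scale" and specifies a chi-squared test, an odds ratio with interval and p-value, and an absolute difference with interval.

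Section 4.3 applies the same methods to GOSE at 12 months, and section 3.0 carries the approach to 24 months. Section 4.5 makes no multiplicity adjustment, on the ground that there is one primary outcome. Section 1.0 says the SAP is written "to avoid post hoc decisions that may affect the interpretation of the results of the statistical analysis".

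**The concern.** The rule depends on the data, and one of its two branches is unfinished. When the fit holds, the common odds ratio with its interval and p-value is the result. When it is rejected, attention moves to a description, and the SAP leaves three things open: which estimate carries the conclusion, how the better arm is identified, and what standing the common odds ratio then has.

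Two things are at stake. First, the effect may differ along the scale, for example fewer deaths but more survivors in vegetative state or severe disability. Leading with mortality and leading with favourable outcome could then give different headlines, and the choice would be made with results in hand. Second, a rejected fit becomes a second way to declare a difference at 5% on the same outcome. The single-outcome argument in section 4.5 does not cover two tests on one outcome.

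**Working it through.** **1. The plan's own figure.** Section 2.2 gives 45% v 60% favourable, 80% power, two-sided 0.05, up to 15% loss, total 400.

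n per arm = [1.960·√(2·0.525·0.475) + 0.842·√(0.45·0.55 + 0.60·0.40)]² / 0.15² = 172.8, so 173 per arm and 346 in all. Dividing by 0.85 and rounding up to equal arms gives 408. With unpooled variance the result is 171 per arm, 342 in all, and 403 after loss. The stated 400 is reproduced to within about 2%. Evaluable patients are 200 × 0.85 = 170 per arm.

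**2. What the fit test can show.** Eight GOSE levels with two pooled leave 7 categories and 6 boundaries. A saturated two-arm model has 2 × 6 = 12 parameters and the proportional odds model has 6 + 1 = 7, so the test has 12 − 7 = 5 degrees of freedom. It measures departure from a common odds ratio in any pattern and has no sign.

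**3. Null error of the two routes.** If the two tests were independent, the error would be 1 − 0.95² = 9.75%. Simulation used 3,000 trials per row, 170 per arm, a likelihood-ratio test for the common odds ratio and a deviance test for fit. The distributions are assumed, in order from death to pooled good recovery, because the SAP gives none.

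| Same distribution in both arms (%) | Common OR significant | Fit rejected | Either | Log OR positive, given fit rejected |
|---|---|---|---|---|
| 40, 4, 11, 12, 12, 11, 10 | 5.0% | 6.5% | 11.2% | 44% |
| 25, 5, 25, 15, 12, 10, 8 | 4.8% | 5.1% | 9.7% | 45% |

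After a null rejection, the sign is close to a coin toss.

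**4. How often the branch is reached.** The control arm is the first distribution above, with 12 + 12 + 11 + 10 = 45% favourable. The proportional shift uses OR = (0.60/0.40)/(0.45/0.55) = 1.83. VS is vegetative state and LSD is lower severe disability.

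| Assumed effect of surgery (percentage points) | Fit rejected | Common OR significant | Fit rejected, OR not significant | Favourable-outcome test significant |
|---|---|---|---|---|
| Proportional, 45% to 60% favourable | 4.4% | 88.3% | 0.4% | 78.3% |
| Deaths −10, all to VS/LSD | 44.0% | 14.2% | 37.7% | 5.0% |
| Deaths −20, all to VS/LSD | 97.7% | 42.7% | 55.9% | 5.0% |
| Deaths −20, of which 6 reach favourable | 88.0% | 60.6% | 34.8% | 17.7% |
| Deaths −15, VS/LSD +20, favourable −5 | 97.0% | 9.2% | 88.2% | 15.6% |

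**5. Effect of naming one estimate.** Suppose the common odds ratio decides when the fit is not rejected, the favourable-outcome test decides when it is, and rejection alone counts for nothing. The null error is then (either − fit rejected) + (fit rejected and favourable test significant). In the first null distribution the fit was rejected with a non-significant favourable test in 5.9% of trials, so the error is (11.2 − 6.5) + (6.5 − 5.9) = 5.3%. In the second that figure is 4.5%, so the error is (9.7 − 5.1) + (5.1 − 4.5) = 5.2%.

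Power of the favourable-outcome test at 170 per arm is Φ{[0.15 − 1.960·√(0.49875/170)]/√(0.4875/170)} = Φ(0.819) = 79.4%. This takes the favourable outcome in section 2.2 to be the cut defined in section 4.2.

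**The case against.** The SAP's reasoning has merit. With treatment as the only covariate, identical distributions satisfy proportional odds, so a rejected fit is indeed evidence that the distributions differ. Describing a difference that varies along the scale, instead of forcing one number on it, is a defensible choice made in advance. That stands. It does not supply a direction, a deciding estimate, or an error rate for using both tests.

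Three stronger readings are tempting, and the SAP does not support them.

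- A reader might infer that no estimate at all is pre-specified after rejection. The favourable-outcome odds ratio and absolute difference are fixed whatever the fit test shows, and they have a direction. Mortality at 6 months is also listed in section 2.1. Nor is the common odds ratio withdrawn: section 4.2 says it will be presented and is silent on its standing after rejection. What is missing is the link between these estimates and the branch.
- A reader might infer that rejection is the likely outcome for this intervention. The SAP gives no GOSE distribution by arm and assumes only 45% v 60% favourable, and the rejection frequencies above vary widely with the assumed effect.
- A reader might quote the chance, about 18% to 20% under the null, that at least one of six boundaries reaches p<0.05. That figure is unconditional. The freedom to choose arises only after rejection, and both events together occurred in about 3% to 4% of simulated null trials.

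**Conclusion.** The point holds in a limited form. Section 4.2 has a pre-specified branch without a pre-specified conclusion, which falls short of the SAP's own aim in section 1.0. The sensitivity analysis could fill the gap but has not been given that role.

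The 10% to 11% null error applies if either route is read as a positive result. The text invites that reading for a difference in distribution, but does not say that a rejected fit would be called a benefit. The figure rests on two assumed distributions and 170 per arm, and is close to the 9.75% expected under independence. The 4% to 98% range for reaching the branch rests wholly on assumed effects and is not a forecast. The sample size is not affected. This should be corrected, but it does not invalidate the main analysis when the fit holds.

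**What to change.** Add to section 4.2, before unblinding:

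1. Rejection of the proportional odds fit is not in itself a positive primary result or evidence of benefit.
2. If the fit is rejected, one estimate named in advance carries the conclusion, and the common odds ratio is still reported. The favourable-outcome absolute difference with its 95% confidence interval is a natural candidate, since it is already specified and appears to be the contrast on which the trial was sized.
3. Absolute differences with 95% confidence intervals at all six GOSE boundaries, including mortality, are all reported as descriptive, and none is selected.

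State that the same rule applies to GOSE at 12 and 24 months.

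The cost is a few sentences, one table and less flexible interpretation when effects differ by category. The candidate estimate has a price: where deaths move only into vegetative state or lower severe disability, the favourable-outcome difference is zero by construction, and the mortality change appears only in the descriptive table. The trial team should accept that openly or name another estimate. A Mann-Whitney probability would avoid the proportional odds assumption but add little as a deciding test: in one assumed scenario its test rejected in 36.2% of trials, against 36.7% for the common odds ratio, with the same verdict in 99.5%.

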### 2.2 Statistical Considerations

**Sample size determination:** The total number of patients will be 400 (200 in each arm of the study) for a 15% difference in outcome (increase in favourable outcome from 45% to 60%) (power 80%, 2-sided significance 0.05, loss to follow-up up to 15%).

**Randomisation:** Participants were randomly assigned to either surgical or medical therapy with a 1:1 allocation as per a computer generated randomisation schedule using permuted blocks of random sizes and stratified

by site. The block sizes were not disclosed in order to ensure concealment. Participants were randomised using a central telephone randomisation service. Allocation concealment was ensured, as the service did not release the randomisation code until the patient had reached stage 3 of the protocol.

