### **4.0 DETAILED ANALYSIS PLAN**

#### **4.1 Analysis populations**

The analysis of all outcome (efficacy/effectiveness) measures and adverse events will be performed on the intention to treat (ITT) population, which will be defined as all randomised patients. The only exclusions will be those patients where the outcome data are not available and/or where consent was withdrawn.

A sensitivity analysis will be performed for the primary outcome measure using the per protocol (PP) population. The PP population will be defined as those patients included in the ITT population but excluding any patients where there had been a severe breach of protocol. Such exclusions will be agreed by the Trial Steering Committee ahead of the database being locked and unblinded, and will include, for example, patients where ICP was not monitored.

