#### **4.5 Adjustment for multiplicity**

Adjustment for multiplicity is considered unnecessary since the trial has a single pre-specified primary outcome measure. The secondary outcomes are exploratory and the results will only be interpreted as supportive evidence related to the primary outcome.

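### The SAP gives deaths before discharge no place in the GCS-at-discharge analysis, so as written the comparison would most naturally be made among survivors only

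*SAP*

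**What the plan says.** SAP section 2.1 lists "Glasgow Coma Scale (GCS) at discharge from neurosciences hospital" as a secondary endpoint. Its analysis is set in section 4.2, under the primary outcome: "The Glasgow Coma Scale sum at discharge will be analysed using the same ordinal methodology described above for the GOSE". For the GOSE that method is an unadjusted proportional odds model giving a common odds ratio, 95% confidence interval and p-value. The only rule about GCS categories is "If necessary, adjacent categories will be pooled if there are too few patients with any particular GCS".

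On who is analysed, section 4.1 defines the population as everyone randomised and then says: "The only exclusions will be those patients where the outcome data are not available and/or where consent was withdrawn". The one imputation rule, in section 4.2, concerns patients with "missing values for their baseline covariates to be included in these analyses"; it does not cover outcomes. Section 2.1 lists "Mortality at 6, 12 and 24 months after randomisation" separately, and nothing links it to the GCS analysis. Section 4.5 says of the secondary endpoints: "The secondary outcomes are exploratory and the results will only be interpreted as supportive evidence related to the primary outcome".

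**The concern.** The GOSE method keeps the dead because the GOSE has a level for death. The GCS does not, so the same method behaves differently when carried over. A patient who dies in the neurosciences hospital has no discharge GCS and, under section 4.1, would most naturally be left out.

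The two groups compared are then those who survived under surgery and those who survived under medical management. Treatment may influence who is in each. If one arm keeps alive patients who would have died in the other, and they leave with low GCS, that arm's survivors look worse on average even though no one was harmed. The SAP would report this with an odds ratio and p-value and treat it as support for the primary result. Deaths are unlikely to be rare: section 2.0 describes intracranial hypertension refractory to first-line and second-line treatment.

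**Working it through.** **1. The SAP's own figures.** The SAP has no figure for this endpoint. Its one design calculation (section 2.2: 45% v 60%, 80% power, two-sided 0.05, up to 15% loss) concerns favourable outcome. It reproduces:

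- n per arm = [1.96·√(2·0.525·0.475) + 0.8416·√(0.45·0.55 + 0.60·0.40)]² / 0.15² = (1.384 + 0.588)² / 0.0225 ≈ 173.
- 173/0.85 gives 204 per arm (408 in total); 173 × 1.15 gives 199 (398). The stated total is 400.

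Nothing below depends on it.

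**2. The text.** Three statements combine: the scale has no death level and none is added (4.2); patients lacking the outcome leave the analysis (4.1); no outcome is imputed (4.2). Together they give an analysis conditional on survival to discharge.

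**3. An example by hand (all inputs assumed).** Deaths before discharge are 40% v 25%. The 60% who survive in either arm have the same GCS in both: 3–5, 6–8, 9–12, 13–14, 15 in 5, 10, 25, 35, 25%. The extra 15% kept alive in the second arm mostly have low GCS: 30, 35, 25, 8, 2%.

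- GCS 13 or more among survivors, higher-mortality arm: 0.35 + 0.25 = 0.60.
- Lower-mortality arm: (0.60 × 0.60 + 0.15 × 0.10)/0.75 = 0.375/0.75 = 0.50.
- Odds ratio at this cut: (0.50/0.50)/(0.60/0.40) = 0.67.

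The proportional odds fit over all five groups gives 0.66, although treatment changed no one's GCS. With 200 randomised per arm, a two-sided 5% test would reject in about 47% of trials. This is a harsh assumption about the extra survivors. If they have the same GCS distribution as the rest, the survivors-only odds ratio is 1.00.

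**4. A graded version (all inputs assumed).** One normal severity variable S decides death: a patient dies if S exceeds Φ⁻¹(1 − m), where m is the arm's mortality. GCS is a second normal variable with correlation −ρ to S, cut into ordered categories, with the same cuts in both arms, so treatment affects no survivor's GCS. The proportional odds model is fitted to the expected counts.

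| Deaths before discharge | ρ | Survivors-only OR for better GCS, lower-mortality arm |
|---|---|---|
| 40% v 25% | 0.6 | about 0.77 |
| 40% v 25% | 0.3 | 0.89 |
| 40% v 25% | 0.1 | about 0.97 |
| 40% v 30% | 0.6 | 0.84 |
| 30% v 25% | 0.6 | 0.92 |
| equal | any | 1.00 |

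Changing the GCS cut-points moves these by no more than about 0.01.

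**5. Death as the lowest category.** In the hand example the odds ratios on everyone randomised are:

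- alive at discharge: (0.75/0.25)/(0.60/0.40) = 2.00;
- GCS 13 or more: (0.375/0.625)/(0.36/0.64) = 1.07;
- GCS 15: 0.15 × 0.02 = 0.003 extra, so (0.153/0.847)/(0.150/0.850) = 1.02.

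The common odds ratio is 1.34. It averages unequal values, so proportional odds is strained, and all of the departure from 1 comes from the assumed mortality difference.

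**The case against.** **The exclusion is inferred.** The SAP nowhere says that a death counts as unavailable outcome data, and a reader might take the GOSE method to include death at the bottom. The protocol, not shown here, may also define how the endpoint is collected. This stands as a limit: it would be wrong to say that the SAP states that the dead are dropped. But the SAP adds no such level, and its pooling rule refers only to GCS scores. At best the wording allows two different analyses, and the choice would fall after the data are seen.

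**The bias is conditional.** It needs a difference in deaths before discharge and worse GCS among the extra survivors. The SAP supports neither with a figure. This stands too: a reader might infer that the result will be biased against surgery, but the documents do not show that.

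**The two odds ratios answer different questions.** Seeing a value below 1 among survivors and above 1 with death included, a reader might say that the correct analysis reverses the sign. It does not: the second is a composite of death and consciousness and, in these examples, reflects only the assumed mortality benefit. It is not a corrected estimate of the first.

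**The consequence is limited.** Section 4.5 calls secondary outcomes exploratory, and the result would be read beside the GOSE and mortality, which count every death. That limits the harm, but an endpoint that can point against the arm that saves lives is poor supportive evidence.

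**Conclusion.** The point holds in this form: the SAP fixes an inferential analysis of discharge GCS without saying how deaths before discharge enter it, and read with section 4.1 the comparison is confined to survivors and loses the protection of randomisation.

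Any bias runs against the arm with fewer deaths, provided that its extra survivors have lower GCS. Under the assumed inputs the size ranges from substantial to negligible, and it vanishes when mortality is equal or the extra survivors resemble the others. None of these figures can be derived from the SAP. They show that the problem can matter, not that it did.

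The matter is confined to one exploratory secondary endpoint. The six-month GOSE analysis, the mortality endpoints and the sample size are untouched.

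**What to change.** Add a rule to the GCS paragraph in section 4.2, for example:

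> Patients who die before discharge from the neurosciences hospital form the lowest ordinal category, below GCS 3, and the analysis includes all randomised patients subject to section 4.1. The result is reported as a composite of death and level of consciousness. Pooling of sparse scores is confined to GCS 3 to 15. GCS among patients discharged alive is tabulated by arm beside the number of deaths before discharge, without a p-value.

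This should need no new data, since mortality and time to discharge are already endpoints in section 2.1. The composite has costs: it overlaps with mortality and the GOSE, and it may fit proportional odds poorly, so the goodness-of-fit check and descriptive fallback that section 4.2 sets for the GOSE should be applied here too.

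If the composite is not wanted, the descriptive table alone, labelled as conditional on survival, is acceptable. Either choice should be fixed before unblinding.

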### **4.3 Secondary Outcome Measures**

ICP control

The following will be presented:

- a. Mean ICP after randomisation (in mmHg)
- b. Number of hours with ICP > 25 mmHg after randomisation
- c. Intracranial hypertension index. This is the number of end-hourly measures of ICP > 20 mmHg divided by the total number of measurements, multiplied by 100. The number of end-hourly measures of ICP > 25 mmHg divided by the total number of measurements, multiplied by 100 will also be presented.
- d. Cerebral hypoperfusion index. This is the number of observations of cerebral perfusion pressure of less than 60 mm Hg divided by the total number of measurements, multiplied by 100. Cerebral perfusion pressure is the mean arterial pressure minus the intracranial pressure.

Duration of intensive care and duration of neurosurgical unit stay will be analysed using survival techniques, with Kaplan-Meier survival estimates and logrank tests to compare optimal medical management with surgery (decompressive craniectomy). Results will be presented as unadjusted hazard ratios with corresponding 95% confidence intervals and p-values.

GOSE at 12 months will be analysed using the same statistical methods set out above for the GOSE at 6 months.

